## Abstract

**Background:**

The purpose of this research is to develop and evaluate methods for conducting cluster randomised trials in a primary care database that contains electronic patient records for large numbers of family practices. Cluster randomised trials are trials in which the units allocated represent groups of individuals, in this case family practices and their registered patients. Cluster randomised trials often suffer from the limitation that they include too few clusters, leading to problems of insufficient power and only imprecise estimation of the intraclass correlation coefficient, a key design parameter. This difficulty might be overcome by utilising databases that already hold electronic patient records for large numbers of practices. The protocol describes one application: a study of antibiotic prescribing for acute respiratory infection; a second protocol outlines an intervention in a less frequent chronic condition of public health importance, stroke.

**Methods/Design:**

The objective of the study is to implement a cluster randomised trial to test the effectiveness of an electronic record-based intervention at achieving a reduction in antibiotic prescribing at consultations for respiratory illness in patients aged 18 and 59 years old in intervention family practices as compared with controls. Family practices will be recruited from the practices that presently contribute data to the UK General Practice Research Database (GPRD). Following randomisation, electronic prompts will be installed remotely at intervention practices to promote adherence with evidence-based standards of medical practice. The intervention was developed through qualitative research at non-intervention practices. Data for outcome assessment will be obtained from anonymised electronic patient records that are routinely collected into GPRD. This protocol outlines the proposed study designs, data sources, sample size requirements, analysis methods and dissemination plans. Ethical issues are also discussed.

**Discussion:**

Results from this study will provide methodological evidence concerning the use of electronic patient records and databases for implementing cluster randomised trials in primary care. The study will also provide substantive findings in respect of electronic record-based interventions to reduce antibiotic prescribing in primary care.

**Trial Registration:**

Current Controlled Trials ISRCTN 47558792.

## Background

This protocol aims to develop an application of electronic patient records to the evaluation of health interventions, including their health impacts and effectiveness. We aim to provide 'proof of concept' of the feasibility and utility of implementing cluster randomised trials utilising electronic patient records in a large national primary care database. The specific objectives of the proposal are to develop, and confirm the feasibility of, a resource efficient method for implementing cluster randomised trials in public health and health services research by implementing a cluster randomised trial in a primary care database using routinely collected electronic patient records to evaluate patient outcomes. There will be two interventions that will build on our previous research; one application is in a common acute condition - antibiotic prescribing in respiratory illness; the other is in a less frequent chronic condition of public health importance - stroke. This protocol only concerns the intervention on antibiotic prescribing in respiratory illness. The research will provide guidance for the future conduct of cluster randomised trials using electronic patient records.

In cluster randomised trials, entire areas or health service organisational units are allocated to intervention or control groups, with outcomes evaluated for individuals within each cluster [1]. Cluster randomised trials (CRTs) are increasingly utilised in public health and health services research and are especially important in the evaluation health service and public health interventions [2]. CRT designs may be used to avoid problems of contamination. CRTs also facilitate pragmatic evaluation of the effectiveness of interventions delivered in routine practice settings. In addition, CRTs allow estimation of cluster level elements associated with the efficacy of the intervention. However, compared with studies in which an equivalent number of individual subjects are allocated, CRTs generally have reduced power because of the correlation of individual responses within clusters. The extent of such clustering is not easy to anticipate [1]. Another difficulty is that only small numbers of clusters may be allocated in CRTs because recruiting, intervening in, and collecting data from clusters may be costly [3].

In this proposal, we suggest that these difficulties may be overcome, to a certain extent, by implementing CRTs within the General Practice Research Database (GPRD), a primary care database that includes records from large numbers of practices. The database will provide a sampling frame for the study, it will also provide a mechanism for the electronic capture of data that describes case-mix at baseline and outcome measures pre- and post-intervention. This will be done by randomising, intervening in, and analysing data from family practices already contributing their electronic patient records to the database. The GPRD offers an excellent pre-existing sampling frame with large numbers of practices covering 5% of the UK population [4,5]. Studies conducted in the GPRD should have good external validity, covering a range of geographical and demographic settings and levels of risk. The GPRD also offers ongoing data collection for baseline and outcome measures for all registered patients, offering the potential to implement studies with greater power at lower cost. GPRD can now be linked individually and anonymously to other National Health Service (NHS) datasets. Currently, 304 GP practices in England are participating in this linkage (about 50% of GPRD). Data from the Hospital Episode Statistics (HES) and National Death Certificates (with date and primary and secondary cause of death) will be used for this study.

The substantive application for the research is in antibiotic prescribing. The problem of resistance to antimicrobial drugs is growing and appropriate prescribing of antimicrobial drugs is of great public health importance [6]. Respiratory tract infections (RTI) account for some 300-400 consultations annually per 1000 registered patients [7] and up to 60% of all antibiotic prescribing in family practice [6]. Giving antibiotics to patients with RTIs is often motivated by a concern to meet patient expectations [8] but antibiotics do not provide clinical benefit in a majority of RTIs [6,9-11]. These illnesses are usually brief and self-limiting, complications are unusual even without antibiotics, [6,12] and antibiotics may promote the spread of resistant organisms [13]. GPRD-based research has shown that antibiotic prescribing for respiratory infections in primary care declined between 1995 and 2000, [7,14] but since 2000 antibiotic prescribing for respiratory illness has stabilised [15]. There is a need to develop and implement interventions that endorse evidence-based antibiotic prescribing in family practice [6]. The age range 18 to 59 has been selected for study because the perceived, and actual, risk of serious infective complications is lower than at the extremes of age.

## Methods/Design

### Objective

To implement a cluster trial in GPRD in a common acute condition. This study aims to test the effectiveness of an electronic record-based intervention at achieving a reduction in antibiotic prescribing at consultations for respiratory illness in patients aged 18 and 59 years in intervention practices as compared with controls.

### Practices and allocation

Practices are being recruited through a letter of invitation from GPRD. A record will be maintained of the numbers of practices approached, recruited and analysed. Since data for all practices are collected into GPRD, it will be feasible to compare participating and non-participating practices through analysis of anonymised data in GPRD.

GPRD practices are allocated by minimisation, stratifying for region and list size. Allocation is at KCL to ensure allocation is separated from the process of practice recruitment. Patients will be all registered patients aged 18 to 59 years. There will be no other exclusion criteria, so as to optimise both internal and external validity [16].

### Intervention

Electronic prompts have been developed based on recommended clinical practice guidelines to be activated during consultations for RTI in the selected age range. The electronic prompts promote no antibiotic prescribing, or delayed antibiotic prescribing, instead of the immediate prescription of antibiotics for respiratory tract infections. The prompts specifically incorporate recommendations from the recent NICE guidelines on antibiotic prescribing in respiratory illness [6]. The research also builds on existing work that has identified barriers to reducing antibiotic prescribing [17-19] by designing prompts that briefly address common concerns (e.g. including messages providing evidence regarding likely consequences of delayed prescribing or not prescribing). During consultations with patients presenting with symptoms of respiratory tract infection, primary care professionals will see the prompts which remind them of recommended standards of care in RTI. The prompts will also provide them with supporting information and links to evidence that supports the recommendations, in a format suitable for printing out for patients when appropriate. The decision on whether to follow the treatment suggestions included in the prompt will be at the discretion of the GP. The GP will also be able to terminate display of the prompt at any time. There will be no intervention at control practices. The intervention phase will continue for 12 months at each practice.

The VISION software used by GPRD practices does not presently include any reminders on antibiotic prescribing, so the trial will compare outcomes associated with the new prompts as compared with care with no prompts.

### Intervention development

Intervention requires the development of prompts that encourage primary care professional adherence with recommended processes of care. The first year of the project has included a workstream to develop appropriate interventions consistent with the initial phases of the MRC framework for complex evaluations [20]. The format and content of the messages to be used in the interventions have been developed by a multi-disciplinary grouping comprising the research team and primary care professionals. Interventions are grounded in theoretical models of behaviour change [21,22] and informed by pre-existing evidence including systematic reviews [23,24] and national clinical guidelines as well as qualitative research. The development process was used to explore the extent to which electronic prompts can be used not only to remind GPs of recommended behaviour but also to convince them it will be beneficial and assist them with implementation. Tape-recorded interviews were carried out with a maximum variety sample of GPs (N = 30) from local non-GPRD practices with a variety of characteristics, to identify factors likely to influence successful implementation, and to pilot messages that have been identified as most likely to positively influence prescribing behaviour [25]. Thematic analysis was used to determine the range of likely responses to the proposed intervention and messages, which were then iteratively modified as necessary. The development and design of the prompts are reported in detail by McDermott et al. [25]

### Intervention implementation

Prompts will be downloaded automatically through the DXS Point-of-Care system. DXS (UK) Ltd collects data on usage of the information provided. In order to understand utilisation of the intervention, we will analyse fully anonymised practice-level data on usage of the electronic prompts that comprise the intervention.

Initial evaluation has shown that GPs may either begin their record of the consultation by initiating an antibiotic prescription, or by recording a medical code consistent with respiratory tract infection. The prompts are designed to be sufficiently flexible to be activated either by the start of an antibiotic prescription or by the specification of a medical code. 'Antibiotics' are defined as including all drugs in section 5.1 of the British National Formulary with the exception of anti-tuberculous and anti-leprotic drugs. Initially, prompt activation will be by means of medical codes.

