### Outcomes and analysis

Outcome evaluation will be through analysis of routinely-collected GPRD data during a defined study period, while historical information will be used to assess the baseline characteristics of the study patients. Information routinely collected into GPRD for all registered patients includes medical history, use of medicines, hospitalisations and other resource use, smoking history, laboratory tests, letters from specialists or hospitals. GPRD also now links patients in GPRD to the English Hospital Episode Statistics, with detailed information on date, duration and reason for hospitalisation. Availability of data for all registered patients has potential to minimise biases from patient selection/recruitment.

Electronic patient records will be eligible for trial analyses if they describe patients who consult with acute respiratory tract infections, defined using pre-specified Read codes that identify conditions appropriate for study, and are aged 18 to 59 years at the date of the consultation. Pre-intervention GPRD analyses have already been reported [15]. Medical codes have been selected for RTIs including sub-groups of colds, rhinitis and upper respiratory infection; sore throat, pharyngitis and tonsillitis; influenza; laryngitis and tracheitis including croup and epiglottitis; acute sinusitis; otitis media and earache; acute bronchitis; and chest infection and pneumonia. The primary outcome will be the proportion of RTI consultations with antibiotics prescribed over 12 months; secondary outcomes will be age- and sex-specific rates of RTI consultation, age and sex-specific proportion of RTI consultations with antibiotics prescribed, and occurrence of RTI complications. We will use linked Hospital Episode Statistics (HES) data for English practices to evaluate hospitalisation with respiratory illness. Analyses will also be reported separately for each sub-group of RTI codes. In order to provide further insight into safety issues, family practices will be offered the opportunity to notify the study team prospectively of suspected adverse events, in fully anonymised format, during the course of the trial.

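### Cheap improvement: the code that fires the prompt also admits the consultation to the primary outcome, so add an antibiotic rate that does not depend on RTI coding

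*Protocol article*

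**What the plan says.** **Trigger.** In the Protocol article, Intervention implementation, the prompts are built so that they can be "activated either by the start of an antibiotic prescription or by the specification of a medical code". The choice for the start of the trial is then fixed: "Initially, prompt activation will be by means of medical codes". The same section reports that some GPs begin the record with the prescription and others with the RTI code.

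**Entry to the analysis.** Under Outcomes and analysis, records are "eligible for trial analyses if they describe patients who consult with acute respiratory tract infections, defined using pre-specified Read codes". The outcome is defined on that set: "The primary outcome will be the proportion of RTI consultations with antibiotics prescribed over 12 months".

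**Arms.** The Intervention section says "There will be no intervention at control practices". For prompted consultations it adds: "The GP will also be able to terminate display of the prompt at any time".

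**Other outcomes.** The "secondary outcomes will be age- and sex-specific rates of RTI consultation", the age- and sex-specific prescribing proportion, RTI complications, respiratory hospitalisation from linked hospital data, and results by RTI code sub-group. Prompt usage is also to be analysed.

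**Data at hand.** "Information routinely collected into GPRD for all registered patients includes medical history, use of medicines".

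**The concern.** The denominator of the primary outcome is created after randomisation by the GP's choice of code. In the intervention arm that choice has a consequence, the prompt. In the control arm it has none. If prompted GPs who intend to prescribe come to omit the RTI code or use a different one, the measured proportion falls although prescribing has not changed. Extra coding of consultations without antibiotics acts in the same direction.

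What is at stake is the meaning of a fall in the primary outcome: less prescribing, or different recording. Among the listed outcomes, those that count antibiotics are confined to RTI-coded consultations, and the others count no antibiotics. Hospitalisation is not coded by the GP but says nothing about prescriptions. Prompt-usage data exist only where there are prompts. Adjustment for pre-intervention prescribing cannot correct coding that changes afterwards. The comparison of control with non-participating practices, described under Limitations, does not look at the intervention arm.

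**Working it through.** **Inputs from Sample size calculation:** control proportion p0 = 0.39; 850 eligible consultations per practice; between-practice coefficient of variation (CV) k = 0.23; alpha 0.05 (taken as two-sided); power 0.80; 50 practices per group planned. **From Background:** RTI accounts for up to 60% of family-practice antibiotic prescribing. **Assumptions, not in the article:** the recoding share x; a CV of 0.2 to 0.4 for the rate outcomes; a baseline correlation r = 0.7 where adjustment is shown; an RTI share s of antibiotics of 40-60%.

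**1. The plan's own figure.** c = 1 + (1.96 + 0.8416)² × [p0(1−p0)/850 + p1(1−p1)/850 + k²(p0² + p1²)]/(p0 − p1)². With p1 = 0.34, c = 47.2; with p1 = 0.33, c = 32.3. The article states 47 and 32, so the variance model is the right one to reuse.

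**2. Shift in the primary outcome with no change in prescribing.** Antibiotic consultations per practice: 850 × 0.39 = 331.5. If a share x loses the RTI code, the observed proportion is 331.5(1−x)/(850 − 331.5x). The false-positive chance uses SE = √{[p0(1−p0)/850 + k²p0² + p1(1−p1)/n1 + k²p1²]/50}, with n1 = 850 − 331.5x and no baseline adjustment.

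| x | Observed proportion | Chance of a significant result (nominal 5%) | Fall in RTI consultation rate (0.39x) |
|---|---|---|---|
| 2% | 38.5% | 6% | 0.8% |
| 5% | 37.8% | 10% | 2.0% |
| 10% | 36.5% | 29% | 3.9% |
| 20% | 33.8% | 85% | 7.8% |

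The full 5-point target appears at x = 0.05/(0.39 × 0.66) = 19.4%, about 64 of 850 consultations per practice.

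**3. What the planned RTI consultation rate would detect.** SE = CV × √(2/50) × √(1−r²).

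| | CV 0.2, r = 0 | CV 0.2, r = 0.7 | CV 0.4, r = 0 | CV 0.4, r = 0.7 |
|---|---|---|---|---|
| SE | 4.0% | 2.9% | 8.0% | 5.7% |
| Power, 3.9% fall (x = 10%) | 16% | 28% | 8% | 10% |
| Power, 7.8% fall (x = 20%) | 50% | 78% | 16% | 28% |

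**4. What a count of antibiotics without an RTI code would add.** The relative rise is x·s/(1−s). At x = 10% it is 15.0% (s = 0.6), 10.0% (s = 0.5) or 6.7% (s = 0.4). Power at CV 0.2 / 0.4 is 96% / 47% for the 15% rise and 38% / 13% for the 6.7% rise unadjusted; with r = 0.7 it is over 99% / 75% and 65% / 21%. At equal CV this rate is more sensitive than the RTI rate when s/(1−s) > 0.39, that is when s > 0.28. The 95% half-width is 1.96 × SE: 7.8% / 15.7% unadjusted and 5.6% / 11.2% adjusted.

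**5. Expected patterns.** Pure recoding lowers the RTI-coded antibiotic rate, raises the not-RTI-coded rate and leaves the total unchanged. A true 5-point effect lowers RTI-coded antibiotics by 0.05/0.39 = 12.8% and the total by 12.8% × 0.6 = 7.7% or 12.8% × 0.4 = 5.1%. The not-RTI-coded rate then stays flat only if the prompts leave non-RTI prescribing alone.

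**The case against.** The strongest reply is that nothing here is an error. The article nowhere reports code omission: it describes the order of entry, lets the GP close the prompt at no apparent cost, and does not say that the trigger codes and the analysis codes are one list. A GP who prescribes first and codes afterwards still enters the denominator but may see the prompt too late, which dilutes the effect and does not exaggerate it. All of that stands. A reader might infer that recoding will occur or that the primary result is biased; the documents support only susceptibility.

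A reader might also infer that the planned outcomes are blind to recoding. They are not. The RTI rate and the prescribing proportion together give RTI consultations with and without antibiotics. With total consultations stable, a true 5-point fall raises the non-antibiotic ones by about 8% (5/61), whereas pure recoding leaves them flat and lowers the total. At the 20% recoding behind the 85% figure, the rate alone has up to 78% power. But both measures rest on the same GP coding, opposite coding shifts can cancel in the rate, and a fall in the rate can be a real drop in consultations.

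The added split has limits of its own. The 60% is a ceiling for all family-practice prescribing, not a figure for ages 18-59 or for same-day RTI codes. Below a 28% share the split is less sensitive than the RTI rate. Wider prescribing restraint could also offset a rise in it. These limits favour the total as the main supportive measure.

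Finally, an analysis plan could add the outcome later from data already held. That is true, and it is why this is a cheap improvement. The article does, however, itself fix the trigger and list the outcomes.

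**Conclusion.** The point holds as a worthwhile, low-cost improvement. With code activation, the recording act tied to the intervention in one arm also decides entry to the primary outcome, and no listed outcome counts antibiotics without an RTI code. The existing check is partial: 8-28% power at 10% recoding and 16-78% at 20%.

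The consequence depends wholly on the recoding share, which the article does not give. At 2% it is negligible; at 10% the false-positive chance is about 29%, and at 20% about 85%, both without baseline adjustment. The power ranges rest further on the assumed CV of 0.2-0.4 and correlation of 0.7. Confidence is medium: the structure is plain in the text, but whether GPs would react in this way is not.

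**What to change.** Keep the primary outcome and the sample size. Add one supportive between-arm outcome from GPRD for all registered patients aged 18-59:

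- BNF 5.1 antibiotic prescriptions, with the exclusions already defined, per 1,000 person-years;
- reported in total (the measure that does not depend on coding) and split by whether an RTI code was recorded the same day;
- adjusted for the practice's pre-intervention rate and given as a rate ratio with 95% CI.

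Read the primary result alongside these estimates and the RTI consultation rate, with no pass/fail rule on the direction of a point estimate. State that an unchanged not-RTI-coded rate is expected under a true effect only if the prompts do not affect non-RTI prescribing. Because the wording on activation leaves a later switch open, record for each practice the date of any change of trigger.

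The cost is one extra query on prescribing records already collected and about two sentences of text. The downside is precision: intervals of about ±6% to ±11% with baseline adjustment, or ±8% to ±16% without, so a null result would not exclude recoding.
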